## 4.2 Participant exclusion criteria

The following are the criteria for exclusion from the study:

1. At risk of HIV infection as mentioned above in the inclusion criteria
2. Active tuberculosis or other systemic infectious process elicited by review of systems, physical examination and laboratory detection (for example detection of Hepatitis B surface antigen or active syphilis)
3. A history of immunodeficiency, ongoing medical and/or psychiatric condition and/or chronic illness requiring continuous or frequent medical intervention
4. Autoimmune disease by history and physical examination
5. Hives or recurrent hives and severe eczema
6. Substance abuse problems (including traditional medicine) during the past 12 months that in the opinion of the investigator would preclude participation
7. History of grand-mal epilepsy, or currently taking anti-epileptics
8. Received blood or blood products or immunoglobulins in the past 3 months.
9. Receiving immunosuppressive therapy such as systemic corticosteroids or cancer chemotherapy
10. Use of experimental therapeutic agents within 30 days of study entry
11. Reception of any live, attenuated vaccine within 60 days of study entry. Medically indicated subunit or killed vaccines (e.g., Hepatitis A or Hepatitis B) are not exclusionary but should be given at least 2 weeks before or after HIV immunisation to avoid potential confusion of adverse reactions.
12. History of cardiac disease including:
  - Previous myocardial infarction (heart attack)
  - angina pectoris; congestive heart failure
  - valvular heart disease
  - cardiomyopathy
  - myo/pericarditis
  - stroke or transient ischemic attack
  - chest pain or shortness of breath at rest or with activity (such as walking up stairs)
  - arrhythmia/episodic palpitations (not excluded: sinus arrhythmia)
  - pacemaker or
  - other heart conditions under the care of a doctor

13. Abnormality in ECG that could indicate risk or make interpretation of vaccine effects difficult according to the study operating procedures. ECG with clinically significant findings, or features that would interfere with the assessment of myo/pericarditis, including any of the following:
  - conduction disturbance (complete left or complete right bundle branch block or nonspecific intraventricular conduction disturbance with QRS >120 ms, an AV block grade II or III, or QTc prolongation [ $> 440\text{ms}$ ])
  - significant repolarisation (ST segment or T wave) abnormality
  - significant atrial or ventricular arrhythmia; frequent atrial or ventricular ectopy (e.g., frequent premature atrial contractions, 2 premature ventricular contractions in a row)
  - ST elevation consistent with ischemia; or evidence of past or evolving myocardial infarction
14. Previously received an HIV candidate vaccine.
15. History of severe local or general reaction to vaccination defined as:
  - **Local:** Extensive, indurated redness and swelling involving most of the major circumference of the arm, not resolving within 72 hours
  - **General:** Fever  $\geq 39.5^{\circ}\text{C}$  within 48 hours; anaphylaxis; bronchospasm; laryngeal oedema; collapse; convulsions or encephalopathy within 72 hours
16. A positive pregnancy test or breastfeeding at screening or enrolment.
17. Study site employees who are involved in the protocol and may have direct access to the immunogenicity results
18. Unlikely to comply with protocol as judged by the principal investigator or his designate.

## 4.3 Number and source of participants

### 4.3.1 Recruitment in Dar es Salaam

A total of 80 volunteers will be recruited from the Dar es Salaam site. They will come from a number of sources, including Police Officers, Prison's officers, and the general public. Police Officers' (PO's) volunteers will be recruited with the assistance of an already established "core group" of about 400 PO's who will assist with educational activities on HIV/AIDS and HIV vaccine studies in the force. The same procedures as in HIVIS-03 and TaMoVac-01 studies will be used, as these have proven useful in avoiding coercion and social discrimination. Meetings at the Police stations, efforts by the "core group" of collaborators and a one to one contact, will be the main modalities to reach potential volunteers. Also volunteers from the Prison force Officers in Dar es Salaam will be addressed for recruitment, first experiences and contacts have been made throughout the TaMoVac I recruitment process. Volunteers will also be sought from the general public including young adults attending the Infectious Disease Clinic (IDC) who would have been assessed by the clinical team regarding their availability for long-term follow up. Information and briefing sessions will be provided after review by the institutional ethics committee to all interested and invited volunteers that will contain general information on HIV and AIDS, HIV Vaccines, and HIV vaccine clinical trials through power point presentations, information sheets, as well as the opportunity for individual questions and counselling. Additionally, volunteers in the ended HIVIS-03 and TaMoVac-01 studies will be asked to assist with recruitment from their respective communities.

### 4.3.2 Recruitment in Mbeya

Volunteers will be recruited from the Mbeya urban environment through advertisement using poster, newspaper advertisement, flyers and local radio. MMRC has developed over the years throughout the past cohort studies a well-established relationship to the

communities. Community leaders and community advisory boards of various areas in the Mbeya region will help in the advertising and recruiting process. Recruitment of the required number of female participants had not been a problem throughout the past study recruitment procedures (RV172, TaMoVac I and RV262). Interested volunteers will be invited to an information and briefing session. These sessions will contain general information through power point presentations about the study. Information sheets as well as the opportunity for individual questions and counselling will be provided. There will also be time for questions on an individual basis without ties to the particular group involved. Interested volunteers will receive an appointment for the first screening visit or contact details for later screening assignment. Information sessions will also be provided for the community leaders and the community advisory board. The briefing and information sessions after review by the institutional ethics committee will take place at the MMRC vaccine trial location in Mbeya and at designated meeting places in communities.

#### **4.3.3 Recruitment in Maputo**

Volunteers will be recruited at the Youth Clinic at HCM. The established Youth Clinic will be used to assist with educational activities on HIV/AIDS and HIV vaccine studies as well as recruitment. Meetings at HCM Youth Clinic, efforts by the “core group” of collaborators and a one to one contact, are the main modalities to reach potential volunteers. The interest in participating in the trial will be expressed individually and anonymously. Information and briefing sessions containing general information through power point presentations about the study, information sheets as well as the opportunity for individual questions and counselling will be offered before and during the trial. Information sessions will also be provided for the community leaders and the community advisory board. The briefing and information sessions after review by the institutional ethics committee will take place at the Youth Clinic at HCM and all study visits at CISPOC. The evaluation of substance abuse will be made through anamnesis (by the study doctor) and through the use of the risk assessment form (Appendix 5). The use of corticosteroids in any medical condition is an exclusion criterion for participation in this study. Volunteers with a history of asthma in the childhood/ adolescence that do not show acute episodes (in adulthood) may be included in the study depending on the clinical evaluation by the study doctors. Volunteers with recurrent asthmatic bronchoconstriction will be carefully evaluated by the medical team to ensure that volunteers who may potentially require treatment with glucocorticoids are not included in the study. If necessary, a pulmonologist can be consulted for a final decision.

#### **4.4 Screening procedures and pre-randomisation investigations**

At the screening visit the volunteer will be allocated a number from the register. The trial will be discussed in detail, and a check of eligibility conducted using a case report form to standardise this procedure. Any questions about the study will be answered. If volunteers are still eligible, willing and interested they will be asked to sign the informed consent form (**Appendix 3**).

To ensure informed consent, volunteers will go through the following processes in detail with a trained member of the study team:

- 1) The rationale of the vaccine trial
- 2) Study timelines, visit schedules and availabilities
- 3) The concept of blinding and randomization
- 4) Pre-HIV risk assessment & discussion
- 5) Safe sex counselling. High quality hypoallergenic condoms will be provided free of charge to volunteers throughout the trial.
- 6) That it is unknown whether or not the study vaccines will protect against HIV infection
- 7) That repeated HIV tests will be performed

- 8) That following immunisation they may develop antibodies that will produce a positive reaction in a routine HIV test, but that provisions have been made to distinguish between a post vaccination response and HIV infection during and after the trial.
- 9) The level of care that will be made available to them should they be found to be HIV infected at any time during their participation in the study, including the screening period.
- 10) That they, or their partner should continue to use a reliable form of contraception for 14 days prior to the immunisation period and for 3 months afterwards
- 11) That they should have no high risk partners and continue to use condoms with sexual partners whose HIV status is not known
- 12) That they may be subject to social risk if they develop HIV antibodies, or by revealing their participation in the study
- 13) The risks and benefits to participate in the trial.
- 14) Risk associated to the study products (vaccines). The concept of safety monitoring and adverse events/reactogenicity reporting will be explained.
- 15) That blood will be taken for safety and immunological tests. The amount of blood will be indicated. Explanations will be provided that tests will be performed at the study sites or at other specialized laboratories in Europe and the US.
- 16) That blood tests might include genetic testing. The risks of genetic testing and how to prevent them within the study will be explained.
- 17) That participants can withdraw study participation at any time without any disadvantages.
- 18) Confidentiality and trial surveillance

Upon this information about the trial and the informed consent procedures, consenting volunteers will be requested to successfully pass a test of understanding (**Appendix 4**) with at least 90% of correct answers with the possibility of maximum 3 repeated attempts.

Study personnel will assess volunteers for past and current risk of HIV infection using the Risk Assessment Questionnaire (**Appendix 5**), followed by counselling for those who will consent to undergo HIV test prior to collecting blood. The counselling process will ensure that volunteers have sufficient knowledge about HIV infection to understand what the test is for, the implications of a positive, negative and equivocal result and the standard of care available for HIV infection locally. They will also be informed on how and when they will receive the result.

After written informed consent has been collected, assessments and investigations will be undertaken according to the schedule in **Appendix 2**. These include demographic, sexual and medical histories, general examination, ECG and collection of urine and blood samples for routine laboratory investigations. Screening investigations for sexually transmitted infections including HIV will be collected (**see section 7.2**).

As soon as the medical report is received and all required test results are available:

- data will be entered onto the screening CRFs and the results of the screening investigations will be reviewed and eligibility signed off by a physician
- completed screening CRFs for all volunteers, whether or not they are eligible will be entered onto the trial database.

Screening will be performed during two screening visits. Additional screening visits to follow-up on medical conditions might be necessary. If more than 3 months have elapsed since the first screening visit, lab examinations (CBC and chemistry) as well as a medical status examination will have to be repeated. The latest visit should be 2-4 weeks before study visit 3, with an HIV serology no older than 8 weeks. If a volunteer is not found to be eligible a Screening Outcome Form will be filled indicating reasons for ineligibility. A study photo identification card will be produced and provided. Finger print identification will be

used at some sites. The photo ID will be kept by the study participant and will have to be presented at each study clinic contact for identification purposes, unless other unequivocal identification can be documented. For screened out volunteers Study ID will be retained. For volunteers enrolled in the study, the photo ID card will be collected at the last study visit and will be replaced by the TaMoVac II certificate on HIV vaccine trial participation (Appendix 7).

## 5 ENROLMENT & RANDOMISATION PROCEDURE

### 5.1 Enrolment

The Enrolment visit (Study Visit 3) will be counted as Week/Day 0 of the study schedule. During the Enrolment Visit confirmation will be made and recorded that the volunteer fulfils all inclusion/exclusion criteria including laboratory results and eligibility criteria using a checklist. If a volunteer is not found to be eligible a Screening Outcome Form will be filled indicating reasons for ineligibility. Enough time has to be planned for the visit so that all questions from the volunteer about the study can be answered or reflected upon. A senior investigator will confirm if the volunteer understands the concepts of the study and will also assess the willingness of the study volunteer to participate. For enrolment the initial screening number will be used as the study number. This means that study numbers may be discontinuous. The participant will then be randomized into one of the Study Groups.

### 5.2 Randomisation

There will be two randomization steps. During the first step prior to any vaccination, participants will be randomized according to different DNA immunizations (Groups 1, 2 or 3) and according to vaccine or placebo (A or B). During the second step prior to MVA, vaccination participants will be randomized according MVA (Group A1) or MVA plus gp140/GLA (Group A2) boosting maintaining the placebo affiliation (Groups B1 or B2). Randomisation lists will be drawn up under the supervision of [name]. These will be stratified by centre and gender to ensure a balance between the three active groups and matched placebos. The assignment for each subject will be placed in an envelope with a unique sequential number. Six sets of plain envelopes will be prepared, two for each centre (for males and females) and couriered to the Study Pharmacist for that centre who will take the prepared envelopes and put them in a box that is kept under lock.

The pharmacist will randomise participants accepted into the study, after receiving a copy of the participant's signed informed consent from nurse/doctor, by selecting the next consecutive envelope containing the vaccine or placebo assignment in accordance with the generated randomization list. The Pharmacist will make a record of the assignment and study number in a register held under lock. In the case a subject has to be replaced this is noted in the register; their assignment should not be given to the next volunteer to be randomized. The next volunteer should be allocated the next assignment. The Pharmacist will then inform the Study Nurse/Medical Officer at the clinic of the randomization group, I – III of the participant, but will not inform on whether this is vaccine or placebo. The Study Nurse/Medical Officer will record the group assignment in the study record of the participant's file. Procedures for the second randomisation will be similar. In addition to centre and gender, allocation will be stratified on the outcome of the first randomisation.

### 5.3 Randomisation codes and unblinding

The vaccines will be kept in the department of Microbiology/Immunology at MUHAS, the study pharmacy at MMRC and the pharmacy at CISPOC under appropriate storage conditions according to manufacturer's specifications. The study pharmacist who has access to the envelopes will draw the study vaccine and the placebo into syringes and label them with the study number, the centre, the randomization group, I to III, date and time and hand them over to the study nurse/study doctor for injection. The study nurse/study doctor administering the vaccines, all other site investigators and lab personnel as well as the participants themselves will be blinded to the allocation of vaccine or placebo.

In the unlikely event that an investigator requests unblinding in order to manage an adverse event, the case will be discussed amongst the Trial Management Group. If a consensus to unblind is reached, then the Study Pharmacist will inform the clinician

managing the event of the allocation, and document this on the pharmacy register. Ideally this individual will be independent of the trial team. Laboratory personnel and other members of the trial team will remain blind to the allocation.

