Participants will be contacted by phone, home visit or clinical contact at the first day following immunization for a brief adverse reaction interview. Additionally, participants will complete diaries over events for the evening of the vaccination day and the 7 days following each vaccination. A diary card (**see Appendix 6**) will be provided after each immunization, with instructions and a full verbal explanation for volunteers to record local and systemic adverse events following immunization, as well as any medication taken. A folder with a diary card, thermometer and a ruler will be issued to each volunteer. The clinical team will provide contact information as well as a telephone number to call 24 hours, in order to assure contact with the study personnel if needed. Furthermore the study clinic will contact participants by phone within 48 hours after each immunization to assure their well being.

All participants will be asked to contact the study site in the case of adverse events of suspected grade 2 or more for evaluation. A decision to offer the participants a visit to the clinic should be made and documented in the source documents. All volunteers with suspected grade 3 or more should be seen by the study physician and documented in the source documents.

Safety follow-up visits are scheduled at week 2 and week 4 after each immunization visit. Diary cards will be reviewed and discussed at the scheduled 2 weeks follow-up visit after each vaccination. Diary entries will be transcribed after revision and discussion with the participant during the follow up visits after each vaccination into a Vaccine/Reaction Form.

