## 11.2 TMG and safety calls during the study

Telephone conference calls will be held every 2-4 weeks and upon request/need. Calls will be organized by the UK MRC Clinical Trials Unit. TMG members will meet through these calls to up-date on the study progress, discuss adverse events, reactogenicity and protocol deviations and assist the site TMT in case management and resolutions. Prepared data management reports will be heard and reviewed. Laboratory and organisational issues will be discussed. Conference call agendas, minutes and follow-ups will be generated and distributed.

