### 15.2 Trial Management Group (TMG)

The supervision of the trial will be a responsibility of the Trial Management Group (TMG). The members will include the Chief Investigator, the Study Chairs, the site Principal Investigators, clinical coordinators, representative from WRAIR and IC, laboratory coordinators and data managers. The TMG will meet through research safety calls as indicated as well as during annual investigator meetings. The TMG will oversee and recommend on the study progress, clinical, data management, laboratory and pharmacy issues as well as study coordination procedures. This committee will be the central body to oversee adverse events and protocol deviations, to generate decisions about grade of adverse events and relationship to study vaccine as well as support for the TMT in case management. The TMG will also be the central body to collect and discuss progress reports on triggering adverse events providing information and recommendations to resume or terminate enrolment and vaccination after study pauses. Notes of TMG meetings will be kept and reported to the TaMoVac Steering Committee and Study Sponsor. Routine reports such as 6-monthly progress reports will be generated by the site PI's or his designee and sent to the the ethical committees and regulatory authorities in Tanzania and Mozambique including notification for the Study Sponsor and the TaMoVac Steering Committee. Expedited reports will be generated by the site PI or his designee and reviewed by the TMG before sending these to the Study Sponsor, TaMoVac Steering Committee, DSMB and to the ethical committees and regulatory authorities in Tanzania and Mozambique.

Members of the TMG are

| Name       | Position                              | Email                     |
|-------------------|----------------------------------------------|----------------------------------|
| [name]   | Chief Investiagtor, MUHAS                    | [contact]        |
| [name]    | Protocol co-Chairand SMI's Medical Expert,KI | [contact] |
| [name]  | MUHAS's Medical Expert                       | [contact]             |
| [name]       | Protocol co-Chair, LMU                       | [contact]                 |
| [name]  | Protocol co-Chair, MRC CTU                   | [contact]            |
| [name]   | Site PI, MUHAS                               | [contact]               |

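### Section 5.3 allows the code to be broken for an adverse event only after Trial Management Group consensus, with no urgent route, time limit or fallback

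*Protocol*

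**What the plan says.** Section 5.3 states who is masked and how the mask may be lifted. The staff giving the injections, the other site investigators, the laboratory personnel and the participants "will be blinded to the allocation of vaccine or placebo". The one unblinding route opens as follows: "In the unlikely event that an investigator requests unblinding in order to manage an adverse event", it continues, "the case will be discussed amongst the Trial Management Group. If a consensus to unblind is reached", "then the Study Pharmacist will inform the clinician" who is managing the event, and notes this in the pharmacy register. Ideally that clinician is independent of the trial team. Laboratory staff and the rest of the trial team stay blind to the allocation.

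Three other sections bear on how this works in practice:

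- **Section 5.2** puts the assignment at the centre: "The Pharmacist will make a record of the assignment and study number in a register held under lock".
- **Section 15.2** describes the Trial Management Group (TMG). Besides the Chief Investigator, study chairs, site Principal Investigators and clinical coordinators, it includes "representative from WRAIR and IC, laboratory coordinators and data managers".
- **Section 11.2** says how the TMG meets: "Telephone conference calls will be held every 2-4 weeks and upon request/need".

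**The concern.** The request in section 5.3 is, by its own terms, made to manage an adverse event. For such a request one expects a route that works at any hour and rests on the judgement of the person looking after the participant. The section instead makes the agreement of a large, dispersed committee a condition of release, and treats urgent and non-urgent requests alike. Read literally, the managing clinician may have to wait for the committee to be assembled and, if it does not agree, will not be told.

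At stake is timely access to one participant's vaccine/placebo allocation when someone responsible for that participant has asked for it. No randomised comparison, type I error rate or power figure is affected.

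**Working it through.** No formula decides this point, so the check sets the relevant sections side by side. One proportion helps to judge its weight.

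**1. Is consensus really a precondition?** Yes. In section 5.3 the pharmacist's disclosure follows only if consensus has been reached. The section states no alternative.

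**2. Does another section supply an urgent route?** None was found.

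- Section 6.2 has immediate hypersensitivity reactions managed under SOPs and gives participants "a telephone number to call 24 hours" to reach study personnel. Neither provision gives access to the code.
- Section 6.6 has each site team manage events and refer those beyond its capacity to hospitals or independent physicians. It does not mention the code.
- Section 7.5.7 sends serious adverse events to the next TMG call.
- Section 7.6 sets an expert review within 3 working days of a suspected serious reaction, and section 8.2 sets 24-hour expedited reporting. Neither concerns release of the code.

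**3. Is there a time limit or a fallback?** Section 5.3 has neither. Section 9.5.3 is a useful contrast: if the TMG cannot agree on the grade of an event or its relationship to product, an expert panel is to be assembled. The protocol therefore foresees that the TMG may fail to agree and provides for it when classifying events, but not when releasing a code.

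**4. How quickly can the TMG act?** Sections 1.1.7 and 15.2 place its members in Tanzania, Mozambique, Sweden, Germany, the United Kingdom and the United States. Regular calls are 2 to 4 weeks apart, with extra calls on request. No quorum and no response time are given, so the wait for an urgent request is undefined.

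**5. Does the location of the code cause the delay?** No. Under section 5.2 the pharmacist at the centre holds the assignment. Any delay comes from the consensus rule.

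**6. What does the code add to what staff already know?** Section 1.1.1 says that clinical staff know the group, whether electroporation is used, and whether one or two injections are given. Only vaccine versus saline is hidden. From Table 1:

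- active: 3 × 60 = 180
- saline: 3 × 6 = 18
- total: 180 + 18 = 198
- chance of active product before any code-break: 180 / 198 = 0.909, or about 91%

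This agrees with the 10:1 ratio in section 9 (10 / 11 = 0.909).

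**7. What does the consensus rule protect?** Section 9.3 bases the analysis on the 180 active participants. The 18 saline recipients are there for blinding and to reinforce that nobody should feel protected. A single logged code-break does not change the comparisons between active groups, and clinical staff know group membership already.

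**The case against.** The strongest reply is that knowing the code would seldom matter. About 91% of participants are on active product, so a clinician can presume exposure. Clinical staff already know the group and the number of injections, and the care described in sections 6.2 and 6.6 does not depend on the code. The documents describe no event in which vaccine versus saline would change urgent care. Section 5.3 itself calls a request unlikely, and section 7.6 expects no serious reactions, although it adds that some elements of the regimen are being used for the first time. All of this stands, and it limits the weight of the point. It does not supply the missing route.

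A second reply is that TMG calls can be held on request and that nothing requires every member to join. This also stands: a reader might infer a wait of 2 to 4 weeks, and section 11.2 does not support that. It guarantees no turnaround either.

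A third is that an emergency contact route may exist in SOPs or in the part of section 8 on reporting procedures at the centres, neither of which was available for this reading. That cannot be excluded, but section 5.3 governs unblinding and points to nothing else.

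A reader might also infer that the route endangers laboratory blinding, because laboratory coordinators sit on the TMG. The text does not support this: the TMG discusses whether to unblind, the allocation goes only to the managing clinician, and section 5.3 keeps laboratory staff and the trial team blind.

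**Conclusion.** The point holds in a narrow form. Section 5.3 makes TMG consensus the sole gateway to a code requested for managing an adverse event. It has no urgent exception, no time limit and no fallback if the group cannot meet or agree. This is a rule as written, not detail left for a later document.

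Its practical size is modest: one binary fact is withheld, and about 91% of participants share the same answer. How many participants might be affected cannot be stated, because the documents give no rate of urgent requests. Nor does the 24-hour telephone number show that the plan anticipates urgent code requests; section 6.2 offers it for contact with study personnel as needed. The conclusion assumes that no emergency route exists in the material not available here.

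The change is still worth making. It serves participant safety, it is cheap, and the rule it relaxes protects little in the planned analysis.

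**What to change.** Amend section 5.3 to separate two kinds of request.

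- **Urgent**, as judged by the clinician managing the event: the site pharmacist, or a sealed code-break held at each centre and reachable out of hours, releases that one participant's vaccine/placebo code to that clinician at once. The break is logged with time, reason and recipient. The TMG and Sponsor are told afterwards that it occurred, but not the allocation.
- **Non-urgent**: TMG discussion and consensus stay as they are.

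The existing statement that laboratory personnel and the rest of the trial team remain blind should apply to both.

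The cost is one paragraph plus out-of-hours access to the code, through the existing pharmacist or the sealed code-break. There are two small downsides. A few code-breaks may prove unnecessary. Knowledge of the allocation could also influence later judgements of relatedness for that participant, which section 7.5.1 assigns to the investigator. Disclosing the code only to the managing clinician, ideally someone outside the trial team as section 5.3 already prefers, limits the second.
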